**Regular monitoring visits:**

Monitoring of the main CRF data will be done on the basis of source data verification of a sample of CRFs (an estimated sample size is 10%). Main focus of the monitoring to be executed is related to the enrollment criteria, the informed consent procedure, safety parameters and the primary endpoint. Exact details will be documented in the monitor plan.

Further activities will involve checks of the Site File, study specific procedures and contact with the site before each visit and contact after the visit regarding unresolved queries.

The sponsor will receive comprehensive monitor reports for every visit within 14 days.

**Close-out visits:**

There will be no separate close-out visits. During the last monitoring visit, the site will be instructed on how to prepare their documentation in such a way that it is ready for long-term archiving. They will also be told about their obligations to keep the applicable documents properly archived over a period of 15 years.

- 1. **Amendments**

Amendments are changes made to the research after a favourable opinion by the accredited METC has been given. All amendments will be notified to the METC that gave a favourable opinion.

Non-substantial amendments (such as typing errors, and administrative changes like changes in names, telephone numbers and other contact details of involved persons mentioned in the submitted study documentation) will not be notified to the accredited METC and the competent authority, but will be recorded and filed by the sponsor.

- 1. **Annual progress report**

The sponsor/investigator will submit a summary of the progress of the trial to the accredited METC once a year. Information will be provided on the date of inclusion of the first subject, numbers of subjects included and numbers of subjects that have completed the trial, serious adverse events/serious adverse reactions, other problems, and amendments.

- 1. **End of study report**

The investigator will notify the accredited METC of the end of the study within a period of 8 weeks. The end of the study is defined as the last patient’s last visit.

In case the study is ended prematurely, the investigator will notify the accredited METC within 15 days, including the reasons for the premature termination. Within one year after the end of the study, the investigator/sponsor will submit a final study report with the results of the study, including any publications/abstracts of the study, to the accredited METC.

- 1. **Public disclosure and publication policy**

Since this is an investigator initiated trial, and no commercial sponsor is involved, no disclosures are warranted. Results will be published in peer reviewed journals and discussed at national and international meetings.

1. **STRUCTURED RISK ANALYSIS**

This is a low to moderate risk study according to the risk classification of the NFU. Both techniques are standard care. Both techniques are executed on large scale within the neurosurgical community since 1949 (FOR) and 1953 (ACDF).

- 1. **Potential issues of concern**

Participation in this clinical study may expose the patient to the following potential risks associated with the two surgical procedures. Due to the surgical procedure the following complications or adverse events could be apparent:

- Death
- Thrombosis
- Pulmonary embolism
- Urinary retention
- Post-operative bleeding / Hematoma
- Post-operative wound infection
- Nerve root injury
- Dural tear
- Post-operative cerebrospinal fluid leakage
- Implant malposition
- Vascular injury
- Blood loss
- Urinary infection
- Spinal cord injury
- Esophagus injury
- Hoarseness
- Pneumonia
- other

The chance of the occurrence of these complications in ACDF is 3-15% and in FOR this is 3-7%. The potential risks are considered rather small but the impact could be high depending on the kind of complication. No extra risk due to the study is anticipated and therefore this study is classified as low to moderate. Comparing these risks to the efficacy data to date, it appears that the benefit of the surgical procedures outweighs the risks.

Anesthesia

The potential risks associated with deep sedation are:

- Allergic reaction
- Nausea or vomiting
- Headache
- Pain and/or bruising at injection sites
- Sore or dry throat and lips
- Blurred and double vision
- Fever

However trained professionals with extensive experience who routinely administer general anaesthesia or local anaesthesia with deep sedation to patients will be responsible for the induction and associated monitoring required for this study.

Radiation

By participating in the study patients will be exposed to radiation during one function X-ray and a MRI and/or CT scan at baseline. The estimated exposure is minimal and will have no consequences for the participating patients.

- 1. **Synthesis**

This study is considered as a low to moderate risk study. It is shown that both surgical techniques are part of care as usual for many years in the participating hospitals and will be conducted by neurosurgeons with excellent expertise and experience with both techniques. The risks associated with the study are largely attributed to the surgical procedure itself and not to the study procedures. Therefore participating in the study does not increase the risk of serious adverse events beyond the risk of undergoing the surgical procedures. We expect that the benefits for the patients will be high and outweigh the risks*.*

1. **REFERENCES**

**Table 1. Time points and calculations for iMCQ and iPCQ**

| **Time points** | **Questionnaire** | **Recall period** | **Multiplication** |
| --- | --- | --- | --- |
| 6 weeks after surgery | iMCQ | 6 weeks | none |
|  | iPCQ | 6 weeks | none |
| 6 months after surgery | iMCQ | 3 months | x 1.5 |
|  | iPCQ | 4 weeks | x 5 |
| 12 months after surgery | iMCQ | 3 months | x 2 |
|  | iPCQ | 4 weeks | x 6.5 |
| 18 months after surgery | iMCQ | 3 months | x 2 |
|  | iPCQ | 4 weeks | x 6.5 |
| 24 months after surgery | iMCQ | 3 months | x 2 |
|  | iPCQ | 4 weeks | x 6.5 |

*Abbreviations:* the Institute for Medical Technology Assessment Medical Consumption Questionnaire (iMCQ), the Institute for Medical Technology Assessment Productivity Cost Questionnaire (iPCQ)

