
HEALTH CARE EFFICIENCY PROBLEM

It is hypothesized that the FOR technique is efficient and lowers the direct and indirect (productivity) costs in comparison with the ACDF technique. The ACDF technique is executed with instrumentation (intervertebral cage), the FOR technique does not require instrumentation and therefore medical costs are lowered when using this technique. The expectation is that the FOR technique leads to earlier and better work participation after operation, however this is an assumption. It could be that because of more neck pain after the FOR treatment, patients remain longer at home and therefore work absenteeism is higher in the FOR treatment group. An important part of this study is to investigate work resumption among CRS patients operated by one of the surgical techniques.

THE INTERVENTION TO BE INVESTIGATED

The ACDF technique is performed through the anterior cervical plane by which the pre-vertebral cervical area can be reached. A discectomy is executed and nerve root decompression will be established. An intervertebral cage is routinely placed to reach fusion on the long term.

The FOR operation is an unroofing technique. By unroofing the foramen of the cervical root, the cervical root is decompressed. The FOR operation is a simple technique with low morbidity and no additional instrumentation (cage, plate, screws) is needed.

EXISTING EVIDENCE OF EFFECTIVENESS

High Risk of bias by morphology in which one of the two techniques is preferred (soft discus compression or osteophytic compression) and surgeon's bias concerning preference for ACDF is present within the literature, concerning the comparison of FOR against ACDF in patients with cervical radiculopathy. No randomized clinical trial (RCT) has been performed comparing both techniques concerning relief of arm pain, cost-effectiveness and work absenteeism.

INNOVATIVE CHARACTER

The innovative value of this trial is threefold:

1) There is insufficient high quality knowledge available which technique has the best outcome for a specific subgroup of patients with a CRS due to a lateral or foraminal compression. No randomized controlled trial has been executed within this group of patients.

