Replacing ACDF by FOR is expected to lower the costs of the treatment procedure by (€7.165 - €4.204) Dutch index price =DOT))= €2.961 per patient. Given that per year approximately 1300 (1:4 of 1700) patients have surgery for lateral root compression, this will lead to savings of €3.849.300 annually for Dutch society as a whole. Literature suggests that FOR may be as effective in relieving arm pain, the proposed study might confirm this. Whether or not this would translate into a better Quality of Life remains to be seen. A potentially very relevant component of a cost-effectiveness analysis from a societal perspective is costs related to reduced work participation. A previous study in patients with non-specific musculoskeletal disorders showed that indirect costs related to reduced work participation may take up to 80% of the total costs. Our literature review, however, revealed that these figures are unavailable for procedures under study in this proposal. The published research that has provided data on work productivity was performed within the context of the US armed services (4). The regulations were very specific (patients who were implanted a cage were mandatorily on sick leave for 6 weeks) and non- transferable to the Dutch social situation. Additionally, relevant data on work resumption are not available in hospital records in the Netherlands. Based on this, we have concluded that there are no data available on which to build a firm efficiency calculation (which would be another argument to perform the proposed study).

The following calculations, therefore, are based on clinical outcomes only, which is less speculative than work participation outcomes based on insufficiently generalizable literature or absent hospital records.

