5. Number or percentage of complications in the short (30 days) and long term period (104 weeks) between the two groups
6. Cost-effectiveness (104 weeks)
7. Budget impact (extrapolated to 5 years)
   1. **Randomisation, blinding and treatment allocation**

Enrolment will be performed in the 6 Centres in the Netherlands. Patients are randomized to either FOR or ACDF. Randomization will be executed per patient per Centre by web based block randomization after the informed consent procedure is fulfilled. The Trial Coordination Centre will facilitate the randomization. Number of inclusions per Centre is described in the patient enrolment plan as described in section 6.3 (study procedures).

- 1. **Study procedures**

If the patient seems to be eligible for a surgical procedure, the patient will be invited for a consultation with the neurosurgeon. He/she will inform the patient about the surgical procedure and the possibility to participate in the FACET study. The neurosurgeon will provide the patient with the study-information.

After one week, the patient can let the neurosurgeon know if he/she wants to participate in the study. Subjects who fulfil the inclusion and exclusion criteria and signed the informed consent will proceed to have the surgical procedure. Before the procedure patients will be clinically evaluated by the surgeon and anesthesiologist to be sure the surgical procedure can be performed. Which procedure is decided by randomization. Randomization will take place before the surgical procedure will be performed and after informed consent is signed. The surgeon and the patient will know to which procedure the patient is randomized. The patient will be admitted to the hospital before the procedure and will be monitored by standard hospital practice before and after the procedure. The patient will be discharged from the hospital if he/she is stable according to the responsible physician. Normally a hospital admission for this procedure takes 2-3 days. The patient will be reviewed at the outpatient clinic at 6 weeks after the surgical procedure, which is standard care. At baseline, 6, 26, 52, 78 and 104 weeks after the surgical procedure the patient is invited to fill out a web based self-administered questionnaire to monitor work ability, arm and neck pain, quality of life, complications and costs according to the visit plan (table 1).

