^f^ Absenteeism is the amount of days that a patient was absent from work times the Dutch reference wage per day. The ‘friction cost method’ was applied, assuming that after a period of 85 days of complete absence, an employee gets replaced by another worker, and productivity would be restored. Presenteeism is the loss of productivity by patients that were not able to fully fulfil their jobs. It was calculated by the proportion of productivity loss of a general working day, times the duration in days, times the average wage per day. Unpaid work is the loss of productivity during unpaid activities such as household work and volunteering. It was calculated by hours a day, times the duration in days, times the Dutch reference price for one hour of unpaid work.

**
[figure not shown]
Figure 1.** **Incremental Cost-Effectiveness Plane comparing Cost Difference and Neck Disability Index from a Societal Perspective.**

*Abbreviations: Multiple imputation sets (MI).*

Figure 1 depicts the cost difference of posterior versus anterior surgery on the vertical axis in Euros, and the difference in Neck Disability Index (NDI) score between groups on the horizontal axis.

**
[figure not shown]
Figure 2. Incremental Cost-Effectiveness Plane comparing Cost Difference and Neck Disability Index from a Healthcare Perspective.**

*Abbreviations: Multiple imputation sets (MI).*

Figure 2 depicts the cost difference of posterior versus anterior surgery on the vertical axis in Euros, and the difference in Neck Disability Index (NDI) score between groups on the horizontal axis.

**
[figure not shown]
Figure 3. Incremental Cost-Effectiveness Plane comparing Cost Difference and Odom Criteria from a Societal Perspective.**

Figure 3 depicts the cost difference of posterior versus anterior surgery on the vertical axis in Euros, and the difference in proportion of Successful Odom Scores between groups on the horizontal axis. A successful Odom score is the proportion of patients graded ‘excellent’ or ‘good’ on the modified Odom criteria, based on patients with complete cost data for all time points and an available Odom score (n=80 in the posterior group and n=73 in the anterior group).

**
[figure not shown]
Figure 4. Incremental Cost-Effectiveness Plane comparing Cost Difference and Odom Criteria from a Healthcare Perspective.**

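### Supplementary Table 1 costs productivity losses for weeks 6–26 from a 4-week recall at week 26, so weeks 6–22 are unmeasured and absenteeism is understated if absence declines over that period

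*Combined protocol and SAP*

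**What the plan says.** Supplementary Table 1 gives the recall period and multiplier for each cost questionnaire. For productivity (iPCQ) the 6-week entry is "iPCQ | 6 weeks | none", so weeks 0–6 are covered in full. The 6-month entry is "iPCQ | 4 weeks | x 5", and the entries at 12, 18 and 24 months are "iPCQ | 4 weeks | x 6.5".

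No iPCQ falls between weeks 6 and 26. Protocol section 6.3 states: "At baseline, 6, 26, 52, 78 and 104 weeks after the surgical procedure the patient is invited to fill out a web based self-administered questionnaire". The week-26 visit has a window of ± 2 weeks, so the recall covers nominal weeks 22–26.

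Footnote f of Supplementary Table 3 defines the cost: "Absenteeism is the amount of days that a patient was absent from work times the Dutch reference wage per day". It applies a friction period of 85 days of complete absence. Presenteeism and unpaid work come from the same questionnaire and carry the same multiplier.

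The documents describe no interpolation from the 6-week answer, no return-to-work date used in costing, and no sensitivity analysis of the multiplier. The cost sections of the protocol do not mention the extrapolation.

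**The concern.** Multiplying the last four weeks by 5 carries the end-of-interval rate back over the preceding 16 weeks. This is unbiased if absence is flat, or if errors happen to cancel. After an operation one would expect absence to fall over these weeks, and the rule then takes its rate from the lowest part of the curve.

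Absenteeism is the largest single row in Supplementary Table 3, at 8,708 euros (posterior) and 8,818 euros (anterior). It makes up 55% and 63% of total productivity losses (8,708/15,797 and 8,818/14,031). Faster return to work is secondary objective 1. If the arms return at a different pace within weeks 6–22, the costing can hide much of that difference or slightly inflate it.

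**Working it through.** **1. The plan's own multipliers.** Multiplier = interval length / recall length. Weeks 6–26: (26 − 6)/4 = 5. Later intervals: 26/4 = 6.5. Coverage: 6 + 4 × 5 + 3 × (4 × 6.5) = 104 weeks. The figures reproduce exactly, with no gap or overlap. What remains open is whether weeks 22–26 can stand for weeks 6–22.

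**2. Single patients** (5 working days a week, absent from surgery, no cap). Rule = days in weeks 0–6 + 5 × days in weeks 22–26.
- Return at week 16: true 16 × 5 = 80; rule 30 + 5 × 0 = 30 (−62%).
- Return at week 8 or week 20: true 40 or 100; rule 30 in both cases.
- Return at week 8 and a new 10-day absence in weeks 23–24: true 40 + 10 = 50; rule 30 + 5 × 10 = 80 (+60%).

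**3. The friction cap.** For a spell starting at surgery, 85 days end at week 85/7 = 12.1 (calendar days) or 85/5 = 17 (working days). Both lie inside weeks 6–22. For a patient returning at week 22, the days lost in weeks 6–22 are 16 × 5 = 80 uncapped, 85 − 30 = 55 with a working-day cap, or 85 − 42 = 43 calendar days (30.7 working days). At the 230 euros per working day given in the protocol introduction, used for scale only, that is 18,400, 12,650 or about 7,060 euros.

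**4. Cohort.** No time course is reported, so the return time T (weeks from surgery) is assumed, with 2 million draws per case and no pre-operative leave. True days = min(5T, cap). Rule days = min(5·min(T, 6) + 25·clip(T − 22, 0, 4), cap). The cap is 85 working days, 85 × 5/7 = 60.7 working days, or none (truncated at week 26).

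| Assumed return curve | Cap | True → rule days (lowest and highest median) | Understated |
|---|---|---|---|
| Exponential, median 6–16 weeks | 85 working days | 37.2 → 25.5; 60.1 → 46.6 | 22–32% |
| Exponential, median 6–16 weeks | 85 calendar days | 32.6 → 23.9; 47.2 → 37.9 | 20–27% |
| Exponential, median 6–16 weeks | none | 41.1 → 27.9; 78.0 → 61.8 | 21–32% |
| Lognormal, median 9–14 weeks, log-SD 0.4–0.6 | 85 working days | log-SD 0.4: 47.8 → 29.7; 67.2 → 35.8 | 36–47% |
| Lognormal, median 9–14 weeks, log-SD 0.4–0.6 | 85 calendar days | log-SD 0.4: 44.8 → 29.5; 55.9 → 33.5 | 31–40% |

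The rule's fivefold inflation of late returners is already in these figures. In the exponential cases 39–45% of workers return in weeks 6–22.

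**5. A different model.** Assume 30–70% absent at week 6 and 5–20% at week 26, with exponential decline. Over weeks 6–26 the rule then recovers 27–84% of true absence uncapped, and 16–79% with the cap. Flat absence gives 100%. Absence rising by 20% gives 107%.

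**6. Difference between arms** (same assumptions as step 4).
- Lognormal medians 9 v 12, log-SD 0.4, working-day cap: true 12.8 days, rule 3.0 (about 23% recovered).
- Exponential medians 12 v 16, calendar cap: true 3.6 days, rule 4.3 (about 120%).
- Exponential, working-day cap: the shortfall is 13.6, 14.3, 14.3 and 13.5 days at medians 8, 10, 12 and 16, so it nearly cancels.

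**The case against.** The case for leaving the rule alone has real substance.

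- **Direction is conditional.** A reader might infer that productivity cost is understated in both arms as a matter of fact. The documents do not show this: they report no absence by time point, and flat absence gives no bias. This objection stands.
- **Absenteeism does not drive the societal difference.** A reader might infer that it does from the size of the row. The reported absenteeism difference is −110 euros, against −3,807 for health care and +1,874 for presenteeism. This stands for the reported figures. It does not settle the matter, because a small difference is also what the rule could produce if the arms diverge in weeks 6–22.
- **The protocol does not place an expected difference in those weeks.** It says "The expectation is that the FOR technique leads to earlier and better work participation after operation", at once calls this an assumption, and allows that more neck pain after FOR could lengthen absence.
- **Pre-operative leave shrinks the effect.** Supplementary Table 2 shows 45 and 55 patients on leave before surgery, 22 and 20 of them beyond 85 days. If the friction period carries over surgery, which is not stated, absence in weeks 6–22 costs nothing for those patients. Assuming 25% have exhausted the cap and 33% have partly used it (uniform over 0–85 days), the shortfall at exponential median 8 falls from 13.6 to 7.5 days. The percentages (20–28%) change little.
- **Other components can offset.** A patient back at week 16 with reduced output in weeks 22–26 is charged presenteeism for all 20 weeks. This was not simulated.
- **Interpolation has its own bias.** Assigning week 14 to every return in weeks 6–22 overstates days by 2–32% in the cases of step 4. Constant-rate scaling is at least transparent. This is a good reason not to replace the base case.

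**Conclusion.** The point holds as a conditional one. That weeks 6–22 are unmeasured, and costed from about weeks 22–26, follows directly from Supplementary Table 1. That absenteeism to week 26 is understated follows only if absence declines between weeks 6 and 26. Decline is plausible after surgery but is not documented.

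The illustrative size is 20–47% of absent days over weeks 0–26. It rests on assumed exponential or lognormal return curves, spells that start at surgery, and no pre-operative leave. It must not be read as an error in the 8,708 and 8,818 euros of Supplementary Table 3, which are 24-month totals.

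For the between-arm difference, and so for the societal cost-effectiveness result, neither size nor sign can be stated. The assumed cases run from about 23% to about 120% of the true difference recovered. The societal result therefore depends on an untested assumption that data already in hand could test.

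**What to change.** Keep × 5 as the stated base case, and state its constant-rate assumption beside Supplementary Table 1. Add a sensitivity analysis that replaces × 5 for weeks 6–26 as follows:

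1. **Paid absence.** For patients absent in the 6-week recall and working in weeks 22–26, treat the return as lying between weeks 6 and 22. Assign the midpoint (week 14), or draw from a fitted return distribution within the existing multiple imputation. The documents do not show whether absence status at the end of week 6 was recorded. If it was not, say how it is inferred.
2. **Presenteeism and unpaid work.** Interpolate between the 6-week and 26-week rates.
3. **Weeks 22–26.** Count them as observed, without multiplication.
4. **Friction cap.** Apply the 85 days to the whole spell, and state whether they are calendar or working days and whether pre-operative leave counts toward them.
5. **Reporting.** Give Supplementary Table 3 productivity losses, total societal costs and the societal cost-effectiveness planes under both methods. Limit the societal conclusion to what holds under both.

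The cost is a re-analysis, with no new data. The downside is that the return curve is assumed and interpolation tends to overshoot (midpoint about 2–32% too high in the simulated cases). The analysis therefore brackets × 5 and does not replace it.
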